## Abstract

**Background:**

Hepatitis A outbreaks in the United Kingdom are uncommon. Most people develop mild to moderate symptoms that resolve, without sequelae, within months. However, in high-risk groups, including those with underlying chronic liver disease (CLD), hepatitis A infection can be severe, with a higher risk of mortality and morbidity. The Health Security Agency and the National Institute of Health and Care Excellence recommend preexposure hepatitis A vaccination given in 2 doses to people with CLD, regardless of its cause. There are currently no published reports of vaccination coverage for people with CLD in England or internationally.

**Objective:**

This study aims to describe hepatitis A vaccination coverage in adults with CLD in a UK primary care setting and compare liver disease etiology, sociodemographic characteristics, and comorbidities in people who are and are not exposed to the hepatitis A vaccine.

**Methods:**

We will conduct a retrospective cohort study with data from the Primary Care Sentinel Cohort of the Oxford-Royal College of General Practitioners Clinical Informatics Digital Hub database, which is nationally representative of the English population. We will include people aged 18 years and older who have been registered in general practices in the Research and Surveillance Centre network and have a record of CLD between January 1, 2012, and December 31, 2022, including those with alcohol-related liver disease, chronic hepatitis B, chronic hepatitis C, nonalcohol fatty liver disease, Wilson disease, hemochromatosis, and autoimmune hepatitis. We will carefully curate variables using the Systematized Nomenclature of Medicine Clinical Terms. We will report the sociodemographic characteristics of those who are vaccinated. These include age, gender, ethnicity, population density, region, socioeconomic status (measured using the index of multiple deprivation), obesity, alcohol consumption, and smoking. Hepatitis A vaccination coverage for 1 and 2 doses will be calculated using an estimate of the CLD population as the denominator. We will analyze the baseline characteristics using descriptive statistics, including measures of dispersion. Pairwise comparisons of case-mix characteristics, comorbidities, and complications will be reported according to vaccination status. A multistate survival model will be fitted to estimate the transition probabilities among four states: (1) diagnosed with CLD, (2) first dose of hepatitis A vaccination, (3) second dose of hepatitis A vaccination, and (4) death. This will identify any potential disparities in how people with CLD get vaccinated.

**Results:**

The Research and Surveillance Centre population comprises over 8 million people. The reported incidence of CLD is 20.7 cases per 100,000. International estimates of hepatitis A vaccine coverage vary between 10% and 50% in this group.

**Conclusions:**

This study will describe the uptake of the hepatitis A vaccine in people with CLD and report any disparities or differences in the characteristics of the vaccinated population.

**International Registered Report Identifier (IRRID):**

PRR1-10.2196/51861

## Introduction

### Overview

Hepatitis A (Hep A) is a viral infection of the liver caused by the hepatitis A virus (HAV). HAV is transmitted through the fecal-oral route, mainly by exposure to contaminated water sources. Hep A outbreaks are uncommon in the United Kingdom, and most people manifest mild to moderate symptoms that tend to resolve, without sequelae, within several months. In high-risk groups, however, such as people with an underlying chronic liver disease (CLD), a superimposed acute infection with HAV can be severe, potentially requiring hospitalization and carrying a higher risk of death. According to the World Health Organization, approximately 100 million Hep A infections occur globally per year, resulting in 15,000 to 30,000 deaths per year [1]. Of these, the number of people with a preexisting CLD diagnosis remains unclear.

CLD largely results from the progressive destruction and regeneration of hepatocytes, leading to fibrosis and cirrhosis, and has a range of etiologies. The most common causes of CLD include alcohol-related liver disease (ALD), chronic hepatitis B (CH-B) infection, chronic hepatitis C (CH-C) infection, and nonalcoholic fatty liver disease (NAFLD), the latter being associated with metabolic syndrome and obesity [2,3]. Deaths in the United Kingdom from CLD have increased annually for the past decade, peaking at 20.6 per 100,000 population in 2020 [4,5], and are expected to surpass the numbers of premature deaths from coronary heart disease [3], CLD-related hospitalizations in the United Kingdom have increased by half, contributing to the £2.1 (US $2.62) billion per year currently spent on treating liver disease [4,6].

The UK’s public health body, the Health Security Agency, and the national guideline body, the National Institute for Health and Care Excellence, recommend preexposure Hep A vaccination to all people with CLD, regardless of the cause [7,8]. The Hep A vaccine series consists of 2 doses, with the second dose at least 6 months after the first.

The data from the United States have shown that less than one-third of at-risk adults receive any vaccination for Hep A, and only one-fifth receive both doses [2,9-12]. Adherence to the vaccination schedule was worse at the extremes of adult age, in ethnic minorities, and in those of low socioeconomic status [10]. The same is true in the United Kingdom; under 35% of eligible people receive the complete Hep A vaccination course, though these data are presented for all eligible patients, regardless of CLD status [13].

Hence, there are no published reports of Hep A vaccination coverage in people with CLD. The purpose of this study is to report Hep A vaccine coverage in people with CLD in UK primary care, with a focus on whether there are disparities as to which people with CLD receive Hep A vaccination.

### Aims

The aim of this study is to report Hep A vaccination coverage in people with CLD in English primary care and the predictors of receiving a single dose or full vaccination course.

### Objectives

The objectives of this study are as follows:

To report yearly Hep A vaccination coverage in people with CLD by:sociodemographic characteristics (eg, age, sex, ethnicity, deprivation, BMI category, smoking status, and alcohol consumption)etiology of CLD (eg, ALD, CH-B, CH-C, and NAFLD).CLD complications (eg, renal disease, ascites, liver failure and transplant, and other cardiometabolic diseases, including diabetes and heart disease)comorbidities and exposures (eg, Cambridge Multimorbidity Score [CMMS], bile duct and colon cancers, at least three doses of COVID-19 vaccine, and flu vaccination).To report the predictors of 1 and 2 doses of Hep A vaccination in people with CLD.

## Methods

### Study Design

This is a retrospective cohort study using data from the nationally representative Primary Care Sentinel Cohort (PCSC) of the Oxford-Royal College of General Practitioners (RCGP) Research and Surveillance Centre (RSC) [14]. The RSC is one of Europe’s oldest sentinel systems, and hepatitis is one of its 32 monitored conditions [15]. The database has previously been used for liver disease and hepatitis research [3,16].

We will use electronic health record data for the period between January 1, 2012, and December 31, 2022. Data will be extracted retrospectively at the time of the beginning of the study.

### Setting

#### Data Source

Data will be extracted from the PCSC of the RSC. The PCSC consists of a nationally representative sample of 7.4 million patients registered in primary care practices in England [17,18]. Pseudonymized data will be extracted from the secure environment of the Oxford-RCGP Clinical Informatics Digital Hub (ORCHID) [19].

#### CLD Ontology and Curated Variables

Key population characteristics, index conditions, and outcomes will be identified using the Systematized Nomenclature of Medicine Clinical Terms (SNOMED CT), in accordance with NHS Digital [20]. To identify these, we will curate data to ensure its use in future studies, supporting the findable, accessible, interoperable, and reusable open science principles [21].

The preliminary SNOMED CT codes to be used to identify CLD as an index condition are summarized in Multimedia Appendix 1. A conceptual model and suitable ontology are developed before carrying out the data extraction [22,23]. The identification of CLD-related concepts will be based on the clinical diagnoses as recorded in primary care; the researchers will not develop ad hoc diagnostic criteria. Clinical codes for CLD will be grouped by their main etiology; a hierarchical ontological approach using the conceptual model will be followed if overlapping concepts are encountered.

#### Data Quality

The RSC has over 55 years of experience in infectious disease surveillance, including vaccination coverage and effectiveness studies [18,24,25]. Viral hepatitis is one of the RSC’s monitored conditions.

### Study Population

We will include adults registered in general practices within the RSC network with a diagnosis of CLD, as defined by our ontology, within the period between January 1, 2012, and December 31, 2022. The following inclusion criteria will be applied: (1) people registered in the RSC general practices, aged 18 years and older, with a diagnosis of CLD; and (2) the ontology for CLD includes ALD, CH-B, CH-C, NAFLD, Wilson Disease, hemochromatosis, autoimmune hepatitis, primary sclerosing cholangitis, and primary biliary cholangitis [2-4].

The following exclusion criteria are applied: (1) patients with recorded contraindications to the Hep A vaccine (confirmed anaphylactic reaction to a previous dose of Hep A containing vaccine or to any of its components); and (2) records of administration of postinfection or risk-of-infection immunoglobulins.

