### Statistical Analysis

#### Reporting Hep A Vaccination Coverage in People With CLD

Hep A vaccination rates will be calculated using the number of vaccinated people with CLD as the numerator and estimates of the CLD population in the ORCHID data set as the denominator. Baseline characteristics of each study group (eg, age and gender) will be summarized using descriptive statistics, including measures of dispersion (eg, SDs and IQRs).

To compare individual characteristics by vaccination status (eg, CLD disease type, sociodemographic characteristics, complications, and comorbidities), we will use descriptive statistics, with pairwise comparisons using the chi-square or Fisher exact tests for categorical variables and the *t* test or Wilcoxon test for continuous variables. If stratification involves more than 2 groups, differences across groups will be tested using the Kruskal-Wallis test for continuous variables and the Pearson chi-square test for categorical variables, followed by pairwise comparisons as above described. All statistical tests will be 2-sided with *P*<.05 considered statistically significant.

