#### Reporting Predictors of 1 and 2 Doses of Hep A Vaccination in People With CLD

##### Overview

A multistate model will be used on a retrospective cohort of individuals identified in the ORCHID diagnosed with CLD. People enter the study on the first diagnosis of CLD, and we will model the transition probabilities between the identified states: diagnosed with CLD, first dose of Hep A vaccination, second dose of Hep A vaccination, and death (Figure 2).

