**Figure 2 figure2:**

State transition diagram for competing risks multistate model for a retrospective cohort of adults with chronic liver disease (CLD) in England between January 1, 2012, and December 31, 2022, evaluating hepatitis A (Hep A) vaccination with 1 and 2 doses as outcomes and death as a competing risk represented as an absorbing state.

A multistate survival model will be fitted to estimate the transition probabilities between the 4 identified study states (Figure 2). The states are (1) diagnosis of CLD, (2) first dose of Hep A vaccination, (3) death, and (4) second dose of Hep A vaccination. The outcome of interest is the Hep A vaccination. Therefore, the state of a second dose of Hep A vaccination is a censored state, with no further transitions to death; the moment a patient receives 2 doses of Hep A vaccination, the follow-up ends. Death is an absorbing state, with no further transitions allowed. Death is included as a competing risk for vaccination, not as an outcome. This means that when calculating the transition probabilities to vaccination, we adjust for when a person is not vaccinated because of death before vaccination rather than for any other predictors of nonvaccination.

Patients lost to follow-up will be right censored and evaluated accordingly as per the likelihood function of the “msm” R package [30].

Multistate probabilities are based on the same assumptions as a Markov process:

The health states considered in the model are thorough and mutually exclusive.The probability to move from one health state to following states only depends on (is conditioned on) the health state of the individual at transition time (memoryless process).Transition probabilities are steady over time.

The state transition probabilities will be estimated conditional on the study risk factors. Study risk factors include (1) etiology of CLD (eg, ALD, CH-B, CH-C, and NAFLD); (2) sociodemographic characteristics (eg, age, sex, ethnicity, deprivation, obesity, smoking, and alcohol consumption); (3) CLD complications (eg, bile duct and colon cancers, renal disease, ascites, liver failure and transplant, and cardiometabolic disease); and (4) comorbidities (eg, CMMS, bile duct and colon cancers, at least 3 doses of COVID-19 vaccine, and flu vaccination).

The multistate model will be estimated using the “msm” (version 1.6.9) package in R [31].

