## Results

The primary care cohort comprised 1704 practices and 7,396,702 registered patients between the January 1, 2012, and December 31, 2022 (Figure 1). We have created an initial clinical code ontology using existing SNOMED CT–curated variables for our sociodemographic variables, hepatitis, and CLD by etiology (Multimedia Appendix 1). The ontology will be expanded to include paraclinical indicators of CLD to identify cases where an explicit diagnosis or specific etiology has not been recorded. Other relevant covariates will be created as required for the study.

The phases of this study will include curating the required variables, conducting our data extraction, statistical analysis, and reporting of the findings through scientific publications.

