## Discussion

### Overview

This study will inform on the state of preventive Hep A vaccination for people with CLD in a representative primary care sentinel network in England. From a total of 7.4 million patients in the RSC network, we will report on the sociodemographic and clinical characteristics of people with CLD with and without Hep A vaccination, for 1 and 2 doses.

The multistate model, adjusted for study risk factors, will identify those associated with having the vaccination. This will inform on the individual characteristics that are associated with an immunization, informing on the subgroups that could benefit from higher engagement with preventive primary care. Any disparities identified could be used to target clinical and public health interventions to improve vaccination coverage in this at-risk group.

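### People with recorded hepatitis A infection or antibody are not identified, so known immunity can be mistaken for a disparity in vaccination

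*Protocol article*

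**What the plan says.** All references are to the protocol article.

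- **Exclusions (Study Population).** There are two. The first reads "The following exclusion criteria are applied: (1) patients with recorded contraindications to the Hep A vaccine", which the article specifies as confirmed anaphylaxis. The second is "records of administration of postinfection or risk-of-infection immunoglobulins".
- **Coverage (Reporting Hep A Vaccination Coverage in People With CLD).** Vaccinated people with CLD are the numerator, with "estimates of the CLD population in the ORCHID data set as the denominator".
- **Entry (Reporting Predictors, Overview).** "People enter the study on the first diagnosis of CLD". No condition on immunity is attached.
- **Model (text under Figure 2).** The states are CLD diagnosis, first dose, second dose and death. On reasons for not being vaccinated, the text says "we adjust for when a person is not vaccinated because of death before vaccination rather than for any other predictors of nonvaccination". Etiology, age and ethnicity are among the risk factors. Past hepatitis A and antibody status are not.
- **Sensitivity Analysis.** Only the window for the second dose and a possible complete-case analysis are mentioned.
- **Use of the result (Discussion, Overview).** The model is meant to find characteristics associated with immunization, "informing on the subgroups that could benefit from higher engagement with preventive primary care".

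**The concern.** The benchmark in the Introduction is preexposure vaccination. A person whose record already shows hepatitis A or HAV antibody is no longer in that position. Under the stated rules that person nevertheless enters at CLD diagnosis, sits in the coverage denominator, and stays at risk of a first dose until a dose, death or censoring. The only route out that relates to infection is the immunoglobulin exclusion. Two people with the same recorded infection are therefore handled differently according to whether immunoglobulin was given.

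For a plain coverage figure this matters little. For the disparity question it matters more, because the analysis cannot separate people who were not vaccinated from people already known to be immune, even where the record shows which they are. If the second kind is commoner in one ethnic, age or etiologic group, the coefficient for that group can absorb the difference. Adjusting for the listed risk factors does not remove it, because immunity is not one of them. The group could then be named as needing more engagement for the wrong reason.

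**Working it through.** **Inputs.** The article gives no figure for immunity, overall or by group, so there is no planned figure to reproduce. Its only relevant number is expected coverage of 10% to 50% (Study Size). The rest is assumed:

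- *v*: uptake in people not known to be immune, the same in both groups; 30% is used, the midpoint of that range.
- *m*: share known to be immune before any dose (assumed).
- *w*: uptake in known-immune people relative to others, where 0 means never vaccinated and 1 means vaccinated equally often (assumed).

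**Formula.** Apparent coverage = v(1 − m) + w·v·m = v[1 − m(1 − w)].

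The coverage ratio of group B to group A is [1 − m_B(1 − w)] / [1 − m_A(1 − w)]. It does not depend on v. The odds ratio does, modestly.

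**Never vaccinated if known immune (w = 0, v = 0.30).**

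| Known immune, A v B | Coverage A | Coverage B | Odds ratio B/A |
|---|---|---|---|
| 2% v 5% | 0.30 × 0.98 = 29.4% | 0.30 × 0.95 = 28.5% | (0.285/0.715)/(0.294/0.706) = 0.96 |
| 1% v 10% | 0.30 × 0.99 = 29.7% | 0.30 × 0.90 = 27.0% | (0.270/0.730)/(0.297/0.703) = 0.88 |
| 5% v 40% | 0.30 × 0.95 = 28.5% | 0.30 × 0.60 = 18.0% | (0.180/0.820)/(0.285/0.715) = 0.55 |

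**Vaccinated half as often (w = 0.5).** The same three pairs give coverage of 29.7% v 29.25%, 29.85% v 28.5%, and 29.25% v 24.0%. The odds ratios are about 0.98, 0.94 and 0.76.

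**Vaccinated equally often (w = 1), or equal immune shares.** The ratio is 1.00, so there is no bias.

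**First-dose intensity.** As a rough conversion with a constant rate and no deaths, the rate is −ln(1 − coverage) per follow-up period. For w = 0 the three rate ratios are:

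- 2% v 5%: ln(0.715)/ln(0.706) = 0.96
- 1% v 10%: ln(0.730)/ln(0.703) = 0.89
- 5% v 40%: ln(0.820)/ln(0.715) = 0.59

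The multistate model is therefore open to the same distortion as the coverage table.

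**The case against.** Five points can be made for the plan.

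1. **The mechanism is not shown in the documents.** A reader might infer that natural immunity will appear as an ethnic or etiologic disparity. That needs unequal known immunity between groups and lower uptake among the immune, and the article gives evidence of neither. The recommendation it cites covers all people with CLD whatever the cause, with no stated exception for immunity. This stands: the distortion is possible, not established.
2. **The large odds ratio is not an expected size.** A reader might take 0.55 as the likely effect. It assumes that none of a 40% immune group is vaccinated. Only immunity known to the practice could deter vaccination, and that share may be far smaller. This stands, and it is why the small-share cases are shown beside it.
3. **The all-CLD denominator is legitimate.** The objective is coverage among people with CLD, and the recommendation covers that population. Restricting to susceptible people would change the quantity estimated. This stands for the descriptive result but not for the disparity reading.
4. **The state list is not contradicted.** A reader might set the missing immune state against the statement "The health states considered in the model are thorough and mutually exclusive". An immune, unvaccinated person still belongs in the first state, so the list remains exhaustive. The article also says openly that death is the only reason for nonvaccination it handles. This stands.
5. **The detail may lie elsewhere.** The Results section mentions existing "curated variables for our sociodemographic variables, hepatitis, and CLD by etiology", and says that other covariates will be created as needed. Suitable codes may therefore exist. That makes the fix easier, but the exclusions, denominator, entry rule and states are all stated, and none of them uses such codes.

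Exclusion as the main rule could also introduce bias if antibody testing differs by group. That is a reason to confine the change to a sensitivity analysis.

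**Conclusion.** The point holds in a limited form. As written, people with recorded hepatitis A infection or HAV antibody before any dose count as unvaccinated and at risk of a first dose, apart from those removed by the immunoglobulin exclusion. This can produce or enlarge an apparent disparity, provided that known immunity differs between groups and known-immune people are vaccinated less often. Both are assumptions from outside the documents. The size is unknown: over the illustrated range the odds ratio runs from 1.00 (no bias) through 0.96 and 0.88 to 0.55. It is not an error in the all-CLD coverage figure or in the list of states. It is a gap in the disparity analysis that can be partly closed at little cost before the targeting conclusion is drawn.

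**What to change.** 1. Keep all-CLD coverage as the main descriptive result.
2. Add codes for hepatitis A infection and positive HAV antibody to the hepatitis code set.
3. Prespecify a sensitivity analysis of both coverage and the multistate model. Exclude people with such a record before entry and before any Hep A dose. During follow-up, censor at the first such record if it precedes the first dose.
4. Report the number excluded and censored by ethnicity and etiology.
5. State in advance that the disparity conclusion will be qualified if the two sets of results differ.
6. List unrecorded immunity as a limitation.

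The cost is one code list, for a condition group the network already monitors, and one rerun. The downside is that infection and antibody results are incompletely recorded, and testing may differ by group. The correction is therefore partial and could itself be selective. An antibody result may also reflect an unrecorded vaccination, and censoring at a test may be informative. The counts in step 4 let a reader see where records were removed, and the main result stays unaffected.
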